### Sporozoite rate

Sporozoite rate or the proportion of adult female *Anopheles* spp. which are sporozoite positive and captured during the trial will be analyzed using a multi-level (variance components model) constructed on a generalized linear model framework with a Bernoulli likelihood and a logit link function. Random intercepts will be included for each study cluster and the study arm will be included as a fixed effect coded categorically as 0 for arm A and 1 for arm B. A simple model will first be considered an unadjusted analysis which only includes fixed effects for the study arm as described and cluster-level random effects and an intercept. A more fully adjusted model will also be used for analysis to account for the complex sampling design by which mosquitoes are captured for α-CSP ELISA. This model will include fixed effects for the capture method (HLC vs. CDC light trap), collection location (indoors vs. outdoors), time since intervention, and calendar month as a seasonality adjustment. Additional random effects will be considered for the catch team/HLC individual. The models will generally take the form below where *p*_*ij*_ is the probability sporozoite positivity at the individual mosquito level (*i* indexes individual mosquitoes within clusters and* j* indexes clusters), *α* is the global intercept, *X*^*arm*^_*ij*_ is the arm assignment for individual *i* in cluster *j*, *β*_*arm*_ is the arm effect to be estimated, *X*^*HLC*^_*ij*_ represents the individual mosquito being caught by HLC, *β*_*HLC*_ is the effect of HLC catch on sporozoite rate relative to CDC light trap, *X*^*indoors*^_*ij*_ represents the individual mosquito being caught indoors, *β*_*indoors*_ is the effect of being indoors on parity relative to collection happening outside, *X*^*time*^_*ij*_ represents a measure of the continuous time since the start of the trial, and *β*_*time*_ is meant to capture an overarching time trend; this variable can also be interacted with the study arm fixed effect to produce an estimate of the difference in time trend by study arm. *X*^*month*^_*ij*_ represents a series of monthly dummy variables in which individual mosquitoes were caught, and *β*_*month*_ represents the series of monthly intercepts, intended to capture seasonal variation in sporozoite rate. *u*_*j*_ are random intercepts for the cluster and *σ* is the standard deviation of the random intercept distribution:$$\mathrm{logit}({p}_{ij})=\alpha +{X}_{ij}^{arm}{\beta }_{arm}+{X}_{ij}^{HLC}{\beta }_{HLC}+{X}_{ij}^{indoors}{\beta }_{indoors}+ {X}_{ij}^{time}{\beta }_{time}+\sum_{month=1}^{11}{X}_{ij}^{month}{\beta }_{month}+{u}_{j}$$

where the likelihood is of the form:$${y}_{ij}\sim Bernoulli({ p}_{ij})$$

And the random intercepts are assumed to follow a normal distribution:$${u}_{j}\sim N(0,{\sigma }^{2})$$

Model results will be presented as the estimates of *α* and the odds ratio above and the standard deviation or variance of the random effects distribution. 95% confidence intervals for the odds ratio and α estimates as well as *z*-statistics and *p*-values for each coefficient will be presented. Sporozoite rate will be directly estimated as the predicted probability of being sporozoite positive in each month when captured via HLC and in each study arm and indoors and outdoors. 95% prediction intervals for sporozoite rate will also be presented.

### Human landing rate

The analysis of data on human landing/biting rate derived from the capture of adult *Anopheles* spp. mosquitoes via HLC conducted indoors and outdoors near houses overnight will be constructed on a generalized linear model framework with a Poisson likelihood and a log link function. Random intercepts will be included for each study cluster, and the study arm will be included as a fixed effect coded categorically as 0 for arm A and 1 for arm B. A simple model will first be considered an unadjusted analysis which only includes fixed effects for the study arm as described, and cluster-level random effects and an intercept. Additional random effects will be considered for catch date, household, and/or HLC “catcher” and autoregressive terms may also be considered with appropriate lags determined by temporal partial auto-correlation functions. The model will take the form below where *y*_*ij*_ is the count of adult *Anopheles* spp. mosquitoes landing on an individual catcher during a specific night (*i* indexes individual catch-nights within clusters and* j* indexes clusters), *α* is the global intercept, *X*^*arm*^_*ij*_ is the arm assignment for individual *i* in cluster *j*, *β*_*arm*_ is the arm effect to be estimated, *X*^*indoors*^_*ij*_ represents the catch-night observation being indoors and *β*_*indoors*_ is the effect of being indoors on human landing relative to collection happening outside, *X*^*month*^_*ij*_ represent a series of monthly dummy variables in which individual mosquitoes were caught and *β*_*month*_ the series of monthly intercepts. *u*_*j*_ are random intercepts for the cluster and *exposure*_*i*j_ is the number of catch-nights corresponding to the particular *y*_*ij*_ observation (generally this will be equal to one (where it does equal one for all observations the log(*exposure*_*ij*_) term may be omitted)) for catch-night *i* in cluster *j*, *λ*_*ij*_ refers to the *log E(y*_*ij*_*|u*_*j*_*)* and *σ* is the standard deviation of the random intercept distribution:$$\mathrm{log}E\left({y}_{ij}|{u}_{j}\right)=\alpha +{X}_{ij}^{arm}{\beta }_{arm}+{X}_{ij}^{indoors}{\beta }_{indoors}+ \sum_{month=1}^{11}{X}_{ij}^{month}{\beta }_{month}+ {u}_{j}+\mathrm{log}({exposure}_{ij})$$

where the likelihood is of the form:$${y}_{ij}\sim Pois({\lambda }_{ij})$$

And the random intercepts are assumed to follow a normal distribution:$${u}_{j}\sim N(0,{\sigma }^{2})$$

Results will be presented as the incidence rate ratio (IRR), corresponding 95% confidence interval, and *p*-value based on the *z*-statistic. This outcome will also be checked for the distributional assumption that the mean and variance of the outcome are similar after conditioning on cluster (e.g., are the within cluster mean and variance similar); if the variance is substantially larger, a negative binomial likelihood will be considered. Human landing rate will be taken to be the predicted mean landing catch per day in each month disaggregated by arm, and indoors vs. outdoors. 95% prediction intervals will also be calculated.

### EIR

The analysis of the entomological inoculation rate will utilize data derived from capture of adult *Anopheles* spp. mosquitoes caught via HLC or CDC light trap indoors or outdoors only and will follow similar principles to the analysis of total sporozoite-positive mosquitoes. The analysis will be based on Student’s *t*-test. For this analysis, estimates of EIR will be made independently for each cluster by calculating an estimated annual EIR within each cluster according to the following formula.$$EIR= \sum_{i=1}^{n}{30s}_{i}\left\{\begin{array}{c}\frac{\sum_{j=1}^{m}{b}_{ij}}{\sum_{j=1}^{m}{d}_{ij}};if \sum_{j=1}^{m}{d}_{ij}>0\\ 0;otherwise\end{array}\right.$$where EIR equals the number of infected bites per person night per year and *n* represents the number of months of the year. Where collections are not made during the full calendar year because the malaria transmission season is assumed to be short and infectious bites are not expected outside of the transmission season, zero will be substituted for the estimated number of infectious bites per person-day during these months as shown in the formula above. In the formula above, *b* represents the number of mosquitoes captured via HLC on a catch person-night *j* during month i*, s* represents the estimated sporozoite rate for each cluster in month *i*, *d* represents the number of person catch-days for person catch night *j* in month *i* (which will generally be equal to one), and finally, *m* represents the total number of observations (person catch-nights) of HLC conducted. EIR within each cluster will be summarized as a single annualized EIR estimate post-intervention. The cluster estimates of the EIR will be compared across arms using a Student’s *t*-test. Results will be presented as mean annualized EIR and standard deviation of annualized EIR as well as *t*-statistic and *p*-value. 95% CIs for mean parity will also be presented for each arm. Should the distribution of EIR be substantially non-normal a non-parametric test such as the Mann–Whitney *U*-test may be considered.

## Additional analyses

### Individual pooled analysis across sites

Individual pooled analysis across the three trial sites (countries) will be conducted collectively following the completion of all three trials. This analysis will follow similar statistical principles to each analysis specified above. The pooled analysis will likely include a study site specified as a “fixed” effect to allow for examination of effect modification by site. Factors related to malaria prevalence such as housing density, and density of ATSB coverage in addition to others will be examined as possible determinants of the outcomes or modifiers of ATSB effect. Additionally, a standard individual patient data meta-analysis is expected to be conducted using combined data from all sites. Heterogeneity of results from each site will be examined and this will be used to determine if pooling data and joint estimation of effect size are appropriate or if data should be treated only independently by trial site.

## Missing data

### Missing outcome data

Significant effort will be made to reduce missing outcome data by revisiting cohort households multiple times and pre-scheduling follow-up visits where possible. When missing data does arise due to failed monthly outcome assessment, no imputation will be used. Missing outcomes due to participant absence will result in censoring (removal of the previous period of follow-up time if there is a missing outcome). They will also have 2 weeks of the next period follow-up time removed as per the definition of the primary outcome. Two sensitivity analyses will be carried out for the primary outcome. These will be the last observation carried forward (e.g., an assumption that a clinical malaria case identified at the last time point observed would represent subsequent new clinical cases (and follow-up time removal) at each missing time point or that the absence of a clinical case at last observation would indicate no clinical cases observed at any missing time points and full follow-up time). This analysis is consistent with a true intention to treat protocol. A second sensitivity analysis will be to assume that all missing values would have resulted in negative findings thus imputing zero extra unobserved clinical cases across both study arms and assuming full follow-up time. These analyses will only be applied to the intention-to-treat analysis population because the per-protocol study population already assumes that full follow-up (all outcome assessments) occurred. Full reporting of the fraction of missing outcome assessments by study arm will be conducted for the intention-to-treat study population.

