### Sample size

Full details of the sample size calculations are contained in the trial master protocol and study site-specific protocols; the sample size determination is presented here in summary form (Tables 2, 3, and 4).

**Table 2 Tab2:** Sample size for incidence

	Mali	Kenya	Zambia
Clusters per arm (overall)	38 (76)	35 (70)	35 (70)
Trial duration in calendar years (seasonality of FU) (total FU per participant time in months)	2 years (8-month seasons) (16 months FU)	2 years (12-month seasons) (24 months FU)	2 years (6-month seasons) (12 months FU)
α (type 1 error probability for 2-year trial)	0.05 (Haybittle-Peto with one interim analysis)	0.05 (Haybittle-Peto with two interim analyses at approx. 50% and 75%)	0.05 (Haybittle-Peto with one interim analysis)
Power	88%	80%	80%
Baseline incidence of clinical malaria in the target age group	0.40 events per person-year (based on 0.6 incident events during an 8-month malaria season) (5y– < 15y)	0.845 events per person-year during a 12-m malaria transmission season (1y– < 15y)	0.50 events per 6-month malaria season (Jan–Jun) (1y– < 15y)
Reduction in baseline incidence (incidence rate ratio = 0.70)	30%	30%	30%
Coefficient of variation	0.40	0.40	0.40
Assumed loss of person time, including true LTFU plus loss due to exclusion of person time following each treatment with AL	20%	20%	34%
Total person-years required (number enrolled per cluster before loss-to-follow-up)	3850 person-years (obtained by enrolling 38 individuals per cluster to account for loss-to-follow-up, followed for a total of 16 months)	1260 person-years (obtained by enrolling 13.5 individuals per cluster to account for loss-to-follow-up, followed for a total of 24 months)	1610 person-years (obtained by enrolling 35 individuals per cluster to account for loss-to-follow-up, followed for a total of 12 months)

**Table 3 Tab3:** Sample size for prevalence outcomes

	**Mali**	**Kenya**	**Zambia**
Cluster per arm	38	35	35
α (2-tailed)	0.05	0.05	0.05
Power	90%	80%	90%
Baseline parasite prevalence measured by RDT among participants aged 6 months and older	50%	29.0%^a^	50.0%
Reduction in baseline prevalence	30%	30%	30%
ICC = intracluster correlation coefficient (coefficient of variation)	0.16 (cv = 0.4)	0.05	0.10
Non-response	20%	20%	20%
Sample size per cluster (accounting for non-response)	25 (32)	24 (30)	16 (20)
Total sample size per survey round/year (accounting for non-response)	1900 (2432)	1680 (2100)^b^	1120 (1400)

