## Analysis

### Outcome definitions

The primary outcome measure is the incidence rate of clinical malaria cases assessed among people aged 12 months to less than 15 years (≥ 5 to 15 in Mali). A clinical case is defined as having an axillary temperature of ≥ 37.5 °C or self-reported fever within the past 48 h, plus a positive malaria RDT. Incidence rate is defined as the total number of incident malaria cases divided by the total person-time observed among each cohort. Outcome assessment will be conducted on each cohort participant monthly. As malaria treatment drugs will be administered to all positive clinical cases (fever + positive RDT) after monthly case ascertainment, each positive (treated) participant will have 2 weeks of the following month of observation time subtracted from their at-risk person-time to account for the prophylactic effect due to sustained antimalarial drug concentration and hence not being at risk of infection. In individuals who are symptomatic and have a positive RDT test in the month following a positive diagnosis of malaria via RDT and treatment, a positive RDT in the following month may indicate persistence of antigen in the blood after effective treatment rather than true reinfection. In such cases, PCR or microscopy results for a *Plasmodium falciparum* infection will be used to resolve if the positive RDT is a result of persistent antigenemia or a true infection (reinfection/recrudescence). In Mali, only microscopy will be used to resolve such cases. In Kenya and Zambia, PCR results will be used where available, and otherwise microscopy. Where the RDT and either the PCR or microscopy results are both positive in month two and the patient meets the other clinical criteria (patent fever or history of fever in the previous 48 h), these observations will be treated as new clinical cases. To keep field procedures unambiguous, a blood slide will be taken whenever a positive RDT is recorded in Mali. Temporary absences from the study area not resulting in failure to ascertain monthly outcomes will not be considered as reducing individual exposure time. Absences greater than the testing interval (1 month ± 5 days) and/or resulting in the failure to ascertain a monthly test result will be removed from the exposure time—meaning that exposure will only be considered to start 1 month prior to the most recent test result.

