In summary:If a participant is symptomatic and positive by RDT, they are treated and the subsequent 2 weeks of follow-up time are censored.If in the next month the participant is also symptomatic and again positive by RDT, they will be treated and PCR or microscopy will be used to determine if they are considered a case of persistent antigenemia or a true new clinical caseIf PCR or microscopy in month two is positive, they are considered to have contributed the person-time between the previous visit and this visit less than 2 weeks and they are considered to contribute a second case to the numerator; two more weeks of follow-up will be censored following the second positive. In Mali, a person who is a malaria case on the day they re-enter the study does not contribute to the number of cases as no follow-up is associated with the case, i.e., they contribute neither to the numerator nor the denominator until they have contributed follow-up.If PCR or microscopy is negative, then contributed follow-up time between the previous visit and the second visit with the second positive RDT is included (minus 2 weeks) and only one case is included in the numerator; however, two more weeks of follow-up time are censored after the second RDT positive (due to the required treatment).

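### The missing-data section deducts 2 weeks of at-risk time after an absence and cites the primary outcome definition, which deducts 2 weeks only after treatment

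*SAP article*

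**What the plan says.** The SAP article describes person-time at risk for the primary outcome in two places.

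**Outcome definitions (under Analysis).** The 2-week deduction belongs to treated cases: "each positive (treated) participant will have 2 weeks of the following month of observation time subtracted from their at-risk person-time". The reason given is pharmacological: "to account for the prophylactic effect due to sustained antimalarial drug concentration and hence not being at risk of infection". The summary that closes the section repeats the trigger: "If a participant is symptomatic and positive by RDT, they are treated and the subsequent 2 weeks of follow-up time are censored". Absences have their own rule. Time without an ascertained result is dropped, and "exposure will only be considered to start 1 month prior to the most recent test result".

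**Missing outcome data (under Missing data).** The first step is "Missing outcomes due to participant absence will result in censoring (removal of the previous period of follow-up time if there is a missing outcome"). The next sentence goes further: "They will also have 2 weeks of the next period follow-up time removed as per the definition of the primary outcome". It mentions neither a positive test nor treatment.

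Two other places bear on the point. The primary model (Analysis methods, Primary outcome) uses the log of each individual's person-time at risk as its offset. Table 2 describes the planned loss as "Assumed loss of person time, including true LTFU plus loss due to exclusion of person time following each treatment with AL" and names no loss for a deduction after an absence.

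**The concern.** The missing-data sentence claims the authority of a definition that does not contain it. A participant who was absent was neither tested nor treated at that visit, so the prophylaxis rationale does not apply, and no other reason is offered.

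The sentence affects the denominator of the primary outcome. A clinical case found at the return visit stays in the numerator, while 14 of the roughly 30 days that go with it are removed. Each arm's rate is then pushed up according to how often its participants miss a visit and come back. If the arms differ in that respect, which is possible in an open-label trial without sham stations, the bookkeeping alone moves the IRR.

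The article is also the master plan for three site-specific SAPs. An unresolved conflict can be copied into them or settled differently in each. If it is settled after data have been seen, the denominator is no longer pre-specified.

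**Working it through.** The plan states no figure on this point, so there is nothing to reproduce. The check compares the texts and then sizes the difference.

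**Side by side**

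| Question | Outcome definitions | Missing outcome data |
|---|---|---|
| Who loses 2 weeks? | Participants treated after a positive RDT | Participants with an outcome missing through absence |
| Why? | Drug prophylaxis | No reason beyond citing the definition |
| Time credited before the return test | 1 month | 1 month less 2 weeks |

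**One participant.** Visit 1 is negative, visit 2 is missed through absence and visit 3 is negative. A month is taken as 30.44 days.
- Outcome definitions: months 1 and 3 count, 2 × 30.44 = 60.9 days.
- Missing outcome data: 60.9 − 14 = 46.9 days.

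**One arm.** Let K be the number of monthly intervals, m the probability that a visit is missed (independent across visits) and f = 14/30.44 = 0.46. K is 6 for the Zambia season or Kenya's first-year rotation, 8 for the Mali season and 12 for Kenya's second year. The plan gives no value for m, so a range is assumed.
- Months kept under Outcome definitions: A = K(1 − m).
- Months kept under Missing outcome data: B = K(1 − m) − f(K − 1)m(1 − m). A deduction needs a missed visit followed by an attended one.
- Rate inflation: A/B = 1/[1 − f·m·(K − 1)/K].

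For K = 8 and m = 0.10, A = 7.2 and B = 7.2 − 0.46 × 7 × 0.1 × 0.9 = 6.91, so A/B = 1.042. The other values are:

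| m | K = 6 | K = 8 | K = 12 |
|---|---|---|---|
| 5% | 1.020 | 1.021 | 1.022 |
| 10% | 1.040 | 1.042 | 1.044 |
| 20% | 1.083 | 1.088 | 1.092 |

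**Between arms.** The IRR is multiplied by the ratio of the two inflation factors.
- Equal m in both arms: factor 1, no change.
- 20% missed in the ATSB arm and 10% in control: 1.083/1.040 = 1.04 (K = 6) to 1.092/1.044 = 1.05 (K = 12). A true IRR of 0.70 would read about 0.73.
- The reverse, 10% ATSB and 20% control: 1/1.0415 = 0.960 to 1/1.046 = 0.956. A true IRR of 1.00 would read about 0.96.
- 30% against 10%: factor about 1.09 to 1.10.

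**The case against.** **It may be a stray sentence about treated participants.** Because it defers to the outcome definition, that section, with its full rule and rationale, would naturally control. This is a plausible account of how the sentence arose. It does not rescue the text: the preceding sentence is about absences, the word *also* adds to the removal just described, and treatment is not mentioned. An analyst coding from the missing-data section would apply the deduction.

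**Safeguards exist.** The plan reports the fraction of missing assessments by arm, and its second sensitivity analysis assumes full follow-up time with no extra cases. An imbalance would therefore be visible. This stands in part. That sensitivity analysis also restores the whole missed period as case-free, so it does not isolate the effect of the 2 weeks.

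**Stronger readings that the documents do not support:**
- *A large bias.* If every missed visit is isolated and followed by an attended one, with 30-day intervals, inflation is 1/(1 − m/(1 − m) × 14/30). That gives 5.5% at 10% missed and 13.2% at 20%, and a null IRR of 1.055/1.132 = 0.93. This is an upper case. Independent misses give about 4% and 8–9%, and clustered absences give less, because a run of misses triggers one deduction. The 20% loss to follow-up under Withdrawal/follow-up cannot stand in for m, since permanent loss has no next period.
- *A spurious arm effect is to be expected.* Open-label allocation makes unequal attendance possible. Nothing in the article says that it will occur or in which direction.
- *The Mali re-entry rule as a third conflict.* In Mali, a participant who is a case on the day of re-entry is handled so that "they contribute neither to the numerator nor the denominator until they have contributed follow-up". This is a labelled site exception, and the article allows site-specific modifications. It is no part of this error.

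**Conclusion.** The conflict is real and the plan is wrong as written: two rules govern the same person-time in the primary model's offset, and the one in the missing-data section is attributed to a definition that does not contain it. The difference is 14 days for each absence-related missed visit that is followed by an attended one.

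The numerical effect is modest. Arm-level rates rise by about 2%, 4% and 8–9% at 5%, 10% and 20% missed. The IRR is unaffected by equal missingness and moves by about 4–5%, in either direction, at 10% against 20%. These sizes assume independent misses, 6 to 12 monthly visits and the same underlying rate in retained and deducted time. The missed-visit rates are assumptions. The case for correction rests on the contradiction in the primary denominator, not on a large expected bias.

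**What to change.** In Missing outcome data, delete the sentence on the further 2 weeks, or limit it expressly to participants who were treated at the preceding visit. State the post-absence rule once, as Outcome definitions already has it: after a missed assessment, exposure restarts 1 month before the next test result. Have the missing-data section refer to that statement instead of restating it, and carry the same text into the three site-specific SAPs before data lock.

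The cost is a wording change and one line of derivation code. Sample size is not affected, because Table 2 names no loss for a post-absence deduction. The Mali re-entry exception can stay as it is.

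### The rule for missed visits deducts 2 weeks of at-risk time that the primary outcome definition it cites gives only to treated cases, so the primary denominator has two conflicting definitions

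*SAP article*

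**What the plan says.** Two sections of the SAP article set the person-time for the primary outcome.

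**Outcome definitions.** The rate is cases over person-time: "Incidence rate is defined as the total number of incident malaria cases divided by the total person-time observed among each cohort". The 2-week deduction belongs to treated cases: "each positive (treated) participant will have 2 weeks of the following month of observation time subtracted from their at-risk person-time". The reason given is "to account for the prophylactic effect due to sustained antimalarial drug concentration and hence not being at risk of infection". The summary list in the same section repeats the trigger: "If a participant is symptomatic and positive by RDT, they are treated and the subsequent 2 weeks of follow-up time are censored". Absence has its own rule. Time without a test result is removed, and "exposure will only be considered to start 1 month prior to the most recent test result".

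**Missing outcome data.** The first step is "Missing outcomes due to participant absence will result in censoring (removal of the previous period of follow-up time if there is a missing outcome". The next sentence reads: "They will also have 2 weeks of the next period follow-up time removed as per the definition of the primary outcome". It sets no condition on treatment.

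Person-time enters the primary Poisson model as the offset (Analysis methods, Primary outcome).

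**The concern.** The missing-data section cites the primary outcome definition for a deduction that the definition does not contain. An untreated participant who was away and then returned has taken no study antimalarial, so the stated reason for the 2 weeks does not apply. Under Outcome definitions the whole month before the return test is at-risk time. Under Missing outcome data, read literally, about half of that month is discarded, while in Kenya and Zambia a case found at the return visit still counts.

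The offset of the single primary endpoint therefore depends on which section the analyst follows. Under the literal missing-data rule the estimated rate rises with the frequency of absence, whatever the malaria risk. If absence differed between arms, part of that rise would pass into the IRR. Because this is a master plan for three trials and a pooled analysis, the wording can be carried into each site's SAP.

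**Working it through.** **The two rules for one untreated participant** who attends visit 1, is absent at visit 2 and returns at visit 3:

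| Interval | Outcome definitions | Missing outcome data, read literally |
|---|---|---|
| Visit 1 to 2 | removed | removed |
| Visit 2 to 3 | full month counted | month minus 14 days |

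With a month of 30.4 days, the difference is 14/30.4 = 46% of the return interval.

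If the participant had been treated at visit 1, the 2 weeks after treatment would fall in the visit 1 to 2 interval, which is already removed. If treated at visit 3, the outcome definition already takes 2 weeks from the following month. In neither case is a deduction from the return interval needed.

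**Inputs.** From the document: 2 weeks, monthly visits, design IRR 0.70 (Table 2). Assumed: the share of monthly visits missed, *m*, because the document gives none. The plan states no figure for the effect of this rule, so there is nothing to reproduce.

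**Inflation of the rate.** Let *s* be the share of attended visits that follow a missed one. The case count is the same under both rules, so

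inflation = 1 / (1 − *s* × 14/30.4).

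*Independent misses*, *s* = *m*:
- 5%: 1/(1 − 0.023) = 1.024
- 10%: 1/(1 − 0.046) = 1.048
- 20%: 1/(1 − 0.092) = 1.101

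Over only 12 visits the first cannot follow a miss, so *s* = *m* × 11/12. The figures become 1.022, 1.044 and 1.092.

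*Misses in runs* of mean length *r*, *s* = *m*/((1 − *m*)*r*), at *m* = 20%:
- *r* = 2: *s* = 0.125, inflation 1.061
- *r* = 3: *s* = 0.083, inflation 1.040

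**Effect on the IRR.** The IRR is multiplied by inflation(ATSB)/inflation(control).

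| Missed, control | Missed, ATSB | Multiplier | True 0.70 becomes |
|---|---|---|---|
| 20% | 20% | 1.000 | 0.700 |
| 15% | 20% | 1.025 | 0.718 |
| 20% | 15% | 0.975 | 0.683 |
| 10% | 20% | 1.051 | 0.736 |
| 20% | 10% | 0.952 | 0.666 |

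With the 12-visit correction the last two rows give 0.732 and 0.669.

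**Check by simulation.** This used 400,000 participants per arm, 12 visits, independent misses, the post-treatment deduction included, and control rates of 0.845 and 1.0 per person-year. At 20% missed, inflation was 1.094 to 1.095. Under the outcome-definition rule the IRR stayed between 0.704 and 0.709 in every attendance scenario. Under the literal missing-data rule it was 0.673 to 0.676 with 20% missed in control and 10% in ATSB, and 0.737 to 0.740 with these reversed.

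**The case against.** **The sentence may be only a slip.** It refers back to the outcome definition, and an analyst who follows the reference finds only the treatment rule. The opening pronoun may have lost a qualifier such as *treated participants*. This is plausible. But the only antecedent on the page is those with missing outcomes, and the sentence says that they *also* lose the time. On either reading the text needs correcting.

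**Stronger readings that the document does not support:**
- *That every missed visit triggers the deduction.* The rule covers missing outcomes due to absence, and only people who return have a next period to deduct from.
- *That 20% of visits will be missed.* The 20% under Withdrawal/follow-up is loss to follow-up. The 20% to 34% in Table 2 combines such loss with time excluded after treatment. Permanent loss triggers no extra deduction.
- *That all three trials are equally inflated.* In Mali, the summary under Outcome definitions leaves a case found on the day of re-entry out of both numerator and denominator, so the factors above do not carry over.
- *That the primary IRR is biased.* The trial is open-label, so unequal attendance is possible, but nothing in the document predicts it. Even a 10-point gap is modest. At 80% power for an IRR of 0.70, the standard error of the log IRR is about 0.357/2.80 = 0.127, so a shift from 0.70 to 0.669 is about 0.36 standard errors. A shift to 0.718 is about 0.2.

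**Safeguards.** Missing assessments will be reported by arm, both sensitivity analyses can restore full follow-up time at missing time points, and site-specific SAPs follow. These make an unnoticed artefact less likely. None corrects the offset, and the sensitivity analyses also impute outcomes, so they do not isolate the 2 weeks.

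**Conclusion.** The contradiction stands: the missing-data section states a deduction for returning absentees that its own cited source gives only to treated cases, and the primary denominator therefore has two definitions. It is a conflict between two stated rules, so condensation of a longer plan does not explain it.

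Its numerical effect is modest and rests on assumed missed-visit shares. Absolute rates rise by about 2% to 10% for 5% to 20% missed if misses are independent, an assumption towards the upper end. At 20% missed the rise is about 4% to 6% for runs of mean length 3 or 2. The IRR is unchanged with equal attendance. A 10-point gap would take 0.70 to about 0.67 or 0.73. The figures apply most directly to Kenya and Zambia. The case for correction is that the primary offset must have one definition before data lock, not that a bias in the IRR has been shown.

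**What to change.** Delete the sentence under Missing outcome data, or restrict it to participants who were RDT-positive and treated. Deletion is simpler, because the outcome definition already covers treated participants. State the person-time rule once, in the main text of Outcome definitions: the 2-week deduction follows treatment only, and after an absence exposure starts 1 month before the next test result. Have the summary list in that section and Missing outcome data refer to that rule. Keep the Mali re-entry exception explicit, and carry the same wording into the site-specific SAPs.

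The cost is one sentence of SAP text and one line in the person-time derivation. No new data are needed and clinical management is untouched.
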